## Methods

### Study Design

A total of 96 participants consisting of practicing clinicians and final year medical students are provided with 16 clinical scenarios, each with a single question. Figure 1 depicts the study steps. The participants must firstly answer the questions without any supporting evidence. In the second stage of the study, the same set of clinicians are provided with the same 16 clinical scenarios and an SML search system. A bespoke best-match SML search system, called Taskiir, was used to avoid any experience variation from using the well-known PubMed interface, as described by Yoo and Mosa [34]. The participants will be constrained to one of 3, 6, or 9 min to search for suitable evidence and complete the task. The time allocated to each user for each task will change depending on the timing cohort they are assigned to (see Task Order and System Rotation section for details). In total, 2 SML search systems with the same user interface, but with significantly different search performance, will be provided to the participants for alternating questions. In this way, the presearch and postsearch correct answer rate by participant and by system will be captured.

To enable comparison with previous studies, much of the method employed by Westbrook et al [33] is replicated, including the use of 6 of the 8 clinical questions used in that study. The main differences with the Westbrook et al study are (1) the varied and strict time limits set to search and answer each question; (2) the use of medical literature only for evidence, rather than the 6 sources they used; and (3) the use of 2 search systems with different search performance.

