The participant must complete the same 16 tasks in the same order as stage 1; however, the participant must now use Taskiir to help them answer the question and to find evidence to support their answer. Evidence is collected by the participant selecting text, images, or both from the source documents they read. The time allocated to search for each task is set according to the timing cohort the participant belongs to and will be one of 3, 6, or 9 min. The participant is told of the time allocation at the start of each question and a minute-by-minute countdown timer is always visible to the participant; warnings are given 30 seconds before time-out. At time-out, the screen is blocked, and the participant is taken to the task completion screen to enter their final details. Other methods of communicating the time limit were trialed during development of the system. In the end, the above method was chosen because it provided a balance between (1) making the participant aware of the time allocated for each question, (2) avoiding time anchoring (where the participant incorrectly assumed all questions are allocated the same time as the first question), (3) keeping them updated with the time remaining so they do not run out of time without warning, and (4) not distracting the participant with time information (eg, using a second-by-second countdown timer that diverted too much attention away from the task).

As this is the first such study measuring the impact of time variation, a few time limits covering a wide range are required to generate significant differences in the outcomes. A useful starting point to establish these time limits is the average completion time of 6.1 min per question, reported in the Westbrook study [33]. From the same study, the SD, based on the average completion times for each of the 8 questions, across 2 systems, is 3.1 min. Therefore, time limits are set at the average question answer time (6 min) and approximately 1 SD either side of this (3 and 9 min). These limits should induce time pressures for 84% of questions with a 3-min time limit, 50% of questions with a 6-min time limit, and 16% of questions with a 9-min time limit. From previous studies, realistic answer timeframes for busy clinicians should be below 5 min [3,15,35], so the 3 proposed time limit cohorts will encompass this pragmatic indicator of search time suitability.

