### Statistical Analyses

To assess the impact of introducing the SML search system on clinical decision quality (RQ-1), each participant’s answer, both presearch and postsearch, will be coded to right (R) or wrong by comparing the participant’s answer with an expert judged assessment (gold answer) of each task. Samples for which (1) no evidence is captured and (2) no relevant documents are marked (either as essential or helpful), by the participant for their postsearch answer, will be discarded, as the value of the search system cannot be confirmed in these cases. Therefore, the decision quality is defined by the correct answer rate (number of right answers/total sample count (N)). A further detailed analysis will be performed of the collected evidence to identify tasks where the literature may contradict the gold answers. Where this occurs, the task answers will be reviewed by experts and overall correct rates adjusted.

To assess the significance of any change in the proportion of right or wrong answers, the McNemar test will be employed because it is a nonparametric test suited to a binary result, with samples taken at 2 points in time. Nonparametric is a better model to assume, given that the data distribution is unlikely to be regular because of the different medical groupings of participants. The sign test, which is also a nonparametric test, will be used to identify any significant changes to the correct rate. To assess any differences between the participant groups (nurses, doctors, and students), a Chi-square analysis will be performed. The participant’s confidence in their answers will be assessed presearch and postsearch to identify any significant changes relating to search intervention, also using chi-square analysis.

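### Answers from 96 people to the same 16 questions are tested as independent units: the profession chi-square overstates significance when answers correlate within person, and the RQ1 McNemar test does so if the benefit of search varies

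*Protocol article*

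**What the plan says.** The Study Design section gives the numbers: "A total of 96 participants consisting of practicing clinicians and final year medical students are provided with 16 clinical scenarios, each with a single question". Under Procedures (In Stage 2), "The participant must complete the same 16 tasks in the same order as stage 1". Each participant therefore supplies up to 16 presearch/postsearch pairs, and each question up to 96.

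Under Statistical Analyses, the outcome is counted in answers: "the decision quality is defined by the correct answer rate (number of right answers/total sample count (N"). Samples with no captured evidence and no document marked relevant "by the participant for their postsearch answer, will be discarded, as the value of the search system cannot be confirmed in these cases", so 1536 is an upper bound.

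For RQ1, "the McNemar test will be employed because it is a nonparametric test suited to a binary result". The reason given is: "Nonparametric is a better model to assume, given that the data distribution is unlikely to be regular because of the different medical groupings". A sign test on the correct rate is added without stating its unit. For profession: "To assess any differences between the participant groups (nurses, doctors, and students), a Chi-square analysis will be performed".

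The only repeated-measures method in the section is an ANOVA for task number, fatigue and time transitions. It does not cover the tests above.

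**The concern.** McNemar's test deals with the pairing of one person's two answers to one question. It still takes the pairs to be independent of each other. Here they are crossed: 16 pairs share a person and 96 share a question. Being nonparametric does not relax that assumption, so the stated rationale does not support the choice. If the professional groups gain differently from search, that difference is itself a source of the correlation the test ignores.

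The profession comparison is the clearer case. Profession does not vary within a person, so the information comes from 96 people and not from some 1536 answers.

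At stake are the p-value for the first research question and the claim about which professions do better. The article also repeats this set of analyses by time limit and by search system.

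**Working it through.** **1. The answer is the unit.** The Sample Size section states 514 per cohort for 40% versus 50%, 90% power, two-sided 5%. The unpooled formula for two independent proportions gives n = (1.960 + 1.282)² × (0.4×0.6 + 0.5×0.5) / 0.10² = 10.507 × 0.49 / 0.01 = 514.9, which truncates to the stated figure (the pooled variant gives 519). Then 514/16 = 32.1, hence 32 people per cohort and 3 × 32 × 16 = 1536 answers. The plan's figure is thus reproduced as a count of independent answers.

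**2. Profession chi-square.** Design effect DE = 1 + (16 − 1) × ICC. For a 2-df test at nominal 5%, true type I error = exp(−5.9915 / (2 DE)). The ICC is assumed.

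| ICC | DE | effective N | type I error |
|---|---|---|---|
| 0.01 | 1.15 | 1336 | 7.4% |
| 0.05 | 1.75 | 878 | 18% |
| 0.10 | 2.50 | 614 | 30% |

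This formula leaves out question difficulty. Every profession answers the same questions, so difficulty adds to the variance that the chi-square assumes but not to the variance of the group difference, and this works against the inflation. Simulating the crossed design (4000 trials, assumed 32 per profession, participant SD 0.5 logit, question SD 1.0) gave 11.4%; other question spreads gave 8-19%. With participant SD 0.8 the range was 20-34%. At participant SD 0.5 and a very wide question SD of 2, a rerun gave about 5%, so the offset can be complete.

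**3. McNemar.** Only discordant pairs count. Assume 30% are discordant: 0.30 × 1536 = 461, or 4.8 per participant and 28.8 per question. With ICCs for the direction of change, DE = 1 + 3.8 × ICC(participant) + 27.8 × ICC(question), and type I error = 2 × [1 − Φ(1.96/√DE)].

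| ICC participant | ICC question | DE | type I error |
|---|---|---|---|
| 0 | 0 | 1.00 | 5.0% |
| 0.05 | 0 | 1.19 | 7.2% |
| 0.02 | 0.02 | 1.63 | 12.5% |
| 0.05 | 0.05 | 2.58 | 22% |

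**4. Simulation of McNemar** with zero mean change (96 × 16, 4000 trials, participant SD 0.5, question SD 1.0 or 1.5):

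- Only ability and difficulty vary: 4.9-5.2%.
- Change varies between participants, SD 0.5: 8.0-8.7%. SD 1.0: 17-22%.
- Change varies by participant (SD 0.3) and by question (SD 0.3), questions drawn at random: 15.7%.
- In the scenario with participant change SD 0.5 only, a t-test on the 96 participant-level changes held 4.8%. In the scenario with both, a test on the 16 question-level changes held 5.6%.

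**5. Is such variation likely?** The article's background section on previous search studies reports a cited study in which nursing students gained 3 points, while overall correctness rose from 32.1% to 46.3%. The Statistical Analyses section itself expects tasks where the literature contradicts the gold answer. On such tasks search could lower the scored rate.

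**The case against.** A reader might infer that the RQ1 p-values are too small whatever happens. The documents do not support that: pairing removes baseline ability and difficulty, and McNemar then keeps its 5%. Varied professional groups matter for this test only if their gains differ.

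A reader might also cite much larger error rates. Simulated McNemar rejection reaches 28-52% when the benefit varies strongly between questions, but only if the 16 questions count as a random sample. Under Clinical Tasks they were selected on four criteria, and everyone answers all of them. With zero mean change fixed over those 16, rejection was 8.4% (change SD 0.5 by participant and 0.5 by question), 7.3% (0.5 and 1.0) and 4.0% (question variation only, SD 1.0). So the question component applies only if the conclusion is meant to go further. The study aim is worded generally, which points that way.

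The RQ1 conclusion may also survive. The planning rates of 30%, 40% and 50% average 40% against 30% presearch. With 30% discordant, z = 0.10 × 1536 / √461 = 7.2, and after DE 2.58 it is still 7.2/1.61 = 4.5. A 3-point gain would not survive: z falls from 2.1 to 1.3.

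The sign test may be intended on participant-level rates, since Study Design says rates are captured by participant. That reading is open, but it would not repair the named McNemar and chi-square tests.

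Finally, profession is not one of the three research questions, and the 32 per profession is an assumption, because the article sets no profession quotas.

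All of these limits stand. None makes independence of the answers a sound assumption.

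**Conclusion.** The point holds in conditional form. The named tests treat crossed, clustered answers as independent, and the reason given for them does not address this. An unseen analysis plan could add an adjustment, but the article states the tests and a mistaken rationale.

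The profession chi-square is anti-conservative when answers correlate within person, unless wide question differences offset it. McNemar for RQ1 is anti-conservative only if the benefit of search varies between participants, or between questions when generalising beyond the 16; the article gives reason to expect variation of both kinds. All ICCs, SDs, the discordance rate and the profession group sizes are assumptions, so the figures show a range and are not estimates for this study.

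The point should not be extended to the within-subject comparisons of time limit and search system, or to the pre/post confidence chi-square. There, ignoring the pairing can make p-values too large instead.

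**What to change.** - **RQ1:** replace pooled McNemar as the inferential test. Use a participant-clustered McNemar, or a mixed logistic model with crossed participant and question effects that lets the pre/post change vary, or a sign or signed-rank test on the participant-level changes in correct rate. Add a question-level check on the 16 changes if the conclusion is to reach beyond these questions.
- **Sign test:** state that it is run on participant-level rates. Run on answers, it is only the exact form of McNemar.
- **Profession:** compare participant-level correct rates, for example by Kruskal-Wallis, or include profession in the same model.
- **Rationale:** withdraw the nonparametric argument as the ground for choosing the test.

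The cost is analysis wording, modest programming and wider intervals. No design change or new data are needed.

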### Study Aims

The overall aim of this study is to examine the suitability of using a search engine to search scientific literature to enable time-pressured clinicians to make better clinical decisions. To support this assessment, the following 3 research questions (RQs) will be addressed:

RQ1: Does the use of a Web-based scientific literature search system enable clinicians to make better clinical decisions?

RQ2: How does time pressure impact clinical decision quality?

RQ3: Does a significantly better search system, as measured by standard information retrieval (IR) evaluation measures, translate to better and faster clinical decisions?

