These studies show that an evidence search system can be effective to help clinicians make better clinical decisions and that SML may be a helpful component of a broader range of evidence sources; however, they do not confirm whether an SML search system is suitable as a stand-alone system for the same task. Studies conducted where SML was the sole source of evidence include the ones by Hersh et al [17,18]. In their first study, 19 medical students and 8 nursing students answered 3 medical questions each [17]. The correct answer rate improved from 39 (45% [39/87]) correct answers to 66 (76% [66/87]) after searching MEDLINE alone. This is a much higher increase than found in the study by Westbrook et al; perhaps attributable to the questions asked, some of which were examination style, and the 1-hour timeframe to complete the questions. In the second study, 45 medical and 21 nurse practitioner students answered a total of 324 questions [18]. The use of MEDLINE-only search improved correctness from 104 (32.1% [104/324]) correct to 150 (46.3% [150/324]) overall; however, the nursing students showed a small improvement of just 3 percentage points. These studies [17,18] do focus on SML alone; however, the longer allowable answer timeframes and the conflicting results motivate the authors of this study to more tightly control the user study, similar to Westbrook et al, but with enforced time limits and a single evidence source.

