### Sample Size

The 2 largest and most similar studies [16,18], both commenced with a presearch correct answer rate of around 30% (29% and 32%) and a postsearch rate around 50% (50% and 46%). Using this as our basis, we wanted to be able to discriminate between the postsearch correct answer rate between each of the 3 time-constrained cohorts. Therefore, to derive the sample size, we estimated that the correct answer rates might vary evenly by 10 percentage points between each group, starting at no improvement. This creates 3 datasets with average correct answer rates of 30%, 40%, and 50% for the 3-, 6- and 9-min cohorts, respectively. Applying a 2-proportion statistical comparison (ie, a 2-sample, 2-sided equality) [66], between each pair of answer rates and setting statistical power to 90%, error rate to 5%, and equal sample sizes per cohort, the minimum sample size required is 514 per cohort, which equates to 32 people per cohort sitting 16 tasks or 96 people in total.

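### The chi-square planned for nurses, doctors and students under RQ-1 does not isolate whether search helps the groups differently

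*Protocol article*

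**What the plan says.** RQ1 in Study Aims asks: "Does the use of a Web-based scientific literature search system enable clinicians to make better clinical decisions". That is a question about change.

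The RQ-1 paragraphs of Statistical Analyses say that each answer, "both presearch and postsearch, will be coded to right (R) or wrong", is compared with an expert answer, and that "the decision quality is defined by the correct answer rate". For the whole sample the change is tested on paired data: "To assess the significance of any change in the proportion of right or wrong answers, the McNemar test will be employed". A sign test is added.

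For the professional groups there is one sentence: "To assess any differences between the participant groups (nurses, doctors, and students), a Chi-square analysis will be performed". It does not say what is cross-tabulated with group or at which stage. The RQ-2 and RQ-3 paragraphs repeat the analyses by time limit and by search system. The repeated-measures analysis at the end of the section covers task number, fatigue and time transitions. Nowhere is there a by-group paired test or a group-by-stage interaction.

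**The concern.** The plan pairs presearch and postsearch answers for the overall effect but does not carry the pairing into the group comparison. Nurses, doctors and final-year students may well differ in what they know before searching. A test that responds to that difference cannot show whether search helped one group more than another. It may be significant when every group gained the same amount, and it may be silent when a group that started low gained most and caught up.

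Unequal gain is a plausible possibility on the article's own account. Previous Search System Studies cites a MEDLINE-only study in which correctness rose from 32.1% to 46.3% overall, while "the nursing students showed a small improvement of just 3 percentage points". If a group difference is reported under RQ-1, readers are likely to take it as a difference in benefit.

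**Working it through.** **The plan's own figure.** The only sample size stated is 514 answers per time cohort (40% v 50%, 90% power, two-sided 5%). The unpooled two-proportion formula reproduces it: (1.960 + 1.282)² × (0.40×0.60 + 0.50×0.50) / 0.10² = 10.507 × 49 = 514.9. The design supplies 32 × 16 = 512 answers per time cohort. No figure is given for the professional groups.

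**Inputs.** Taken from the article: right/wrong coding at both stages, presearch rates near 30% and postsearch rates near 50% (Sample Size), and 96 × 16 = 1,536 answers in total. Assumed: 512 answers per professional group (a third of 1,536), the group-specific rates, and independent answers.

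**Step 1. Equal gains, unequal starts: postsearch table.** Presearch 40/35/30% with a gain of 10 points each gives postsearch 50/45/40%, mean 45%. The noncentrality of the 2-df chi-square is

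λ = Σ n(p − p̄)² / [p̄(1 − p̄)] = 512 × (0.05² + 0 + 0.05²) / (0.45 × 0.55) = 2.56 / 0.2475 = 10.34.

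Against the critical value 5.99 the rejection probability is 0.829, although the gains are identical.

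**Step 2. Same scenario: change categories.** Cross-tabulate group with right-right, right-wrong, wrong-right and wrong-wrong (6 df, critical value 12.59). If 20% of presearch-right answers turn wrong, the rows are 32/8/18/42%, 28/7/17/48% and 24/6/16/54%, with λ = 15.6 and rejection probability 0.86. If 10% turn wrong, λ = 13.5 and the probability is 0.80. This version also responds to the starting level.

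**Step 3. Smaller spread.** Presearch 29/32/35% with an equal gain of 18 points gives postsearch 47/50/53%: λ = 512 × 2 × 0.03² / 0.25 = 3.69, rejection probability 0.39. With unequal group sizes it falls to 0.28 (256/768/512 answers) and 0.21 (160/960/416 answers, simulated).

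**Step 4. Unequal gains that end level.** Presearch 25/30/35% with gains of 20/15/10 points gives 45% in every group. Then λ = 0 and the postsearch chi-square rejects 5% of the time. A 2-df test of gain, with variance (discordance − gain²)/512 per group, has power 0.79, 0.64 and 0.54 if 30%, 40% or 50% of answers change between stages.

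**Step 5. Simulation.** 4,000 runs per setting, 1,536 answers, 20% of presearch-right answers turning wrong. The ranges run over group splits 512/512/512, 256/768/512 and 160/960/416. Entries are rejection rates at the 5% level.

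| Presearch % | Gain (points) | Postsearch chi-square | Change-category chi-square | Test of paired gain |
|---|---|---|---|---|
| 25/35/40 | 15/15/15 | 85-99% | 89-100% | 5% |
| 29/32/35 | 18/18/18 | 21-39% | 21-41% | 5% |
| 25/35/40 | 23/13/8 (all end at 48%) | 5% | 88-100% | 83-99% |
| 32/32/32 | 3/17/17 | 86-100% | 96-100% | 96-100% |

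With no group difference at all, every test rejects in about 5% of runs. Only the paired-gain test stays near 5% when gains are equal and rises when they are not.

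**The case against.** The case against has several good parts.

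- **The table is not fixed.** A reader might infer that the plan prescribes a chi-square on right/wrong at one stage. The sentence does not say so, and the next sentence of the section uses chi-square for a pre-to-post change in confidence. A change-category table is therefore open, and it does detect the catch-up case (88-100%). This stands. It does not rescue the analysis, because that table also rejects when gains are equal and starts differ.
- **Levels may be what is meant.** The wording covers differences of any kind, and a comparison of correct rates is legitimate description. This stands too. The mismatch comes from its place under RQ-1 with no group comparison of gain beside it.
- **A reader might infer that the test measures knowledge instead of benefit.** That is too strong. A postsearch table mixes the two and does reflect gain when presearch rates are equal (86-100% in the last row of the table).
- **A reader might infer that comparing gain by profession is a study aim, or that providers will choose systems by profession.** The documents support neither. None of the three research questions compares professions, the nursing-student result is background, and the significance section does not speak of selection by profession.
- **An article leaves detail to a fuller plan.** That would excuse an unspecified table. Here a test is named, and neither reasonable version of it isolates differential gain.

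**Conclusion.** The point holds in limited form. Neither a right/wrong chi-square nor a change-category chi-square isolates whether the gain from search differs between nurses, doctors and students, and no other stated analysis does. The postsearch version can err in both directions; the change-category version errs when gains are equal but starts differ.

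The size is illustrative. It rests on assumed group sizes, since the sample is a convenience sample with no stated mix, on assumed group rates, and on independence between answers. In the scenarios examined, with equal gains and unequal starts, the postsearch test rejects from about 21% to 99% of the time. The 5% figure for missed differences belongs to the special case in which unequal gains exactly cancel unequal starts. Each participant gives 16 answers, and correlation between them would change all these figures; that is a separate matter from the one raised here.

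This is a secondary comparison. The overall RQ-1 test of change is paired and is not affected by this point. The correction is worth making because it is cheap and prevents a misreading.

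**What to change.** In the RQ-1 part of Statistical Analyses, replace the group chi-square with a comparison of the paired pre-to-post change between nurses, doctors and students. In practice this is a test of the group-by-stage interaction in a model that allows for repeated answers from the same participant (for example, participant as cluster). State the scale on which gain is compared; the working above uses percentage points. Report each group's presearch rate, postsearch rate and gain, with a confidence interval for the gain. Keep comparisons of correct rates between groups, and say that they are descriptive.

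The cost is a change of wording and slightly more analysis work. Both sets of answers are already collected from every participant, so no new data are needed. The drawback is low precision if one group turns out small, which the intervals would show.

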### Clinical Tasks

The criteria for task selection was that each task must (1) have answers able to be found in the literature, (2) be able to be answered with yes/no/conflicting information or a single-term/phrase response, (3) be credible to a practicing clinician, and (4) have nonobvious answers. Overall, 6 of the 16 clinical questions are those produced and used by Westbrook et al [16] and are reproduced here in Table 2. The tasks consist of real-life scenarios and a clinical question for each scenario. Westbrook et al derived the tasks using clinical experts and designed them to be clinically relevant and of mixed complexity. In addition, 4 questions are sourced from Hersh et al [18], which are also clinical questions and used for the same purposes as this study. Overall, 3 questions are modified from the text retrieval conference (TREC) 2015, clinical decision support (CDS) topic set [37]. These questions were provided with diagnoses, which our medical physician (DA, MBBS), modified into a question of a similar format to the other questions. Finally, our medical physician also devised a further 3 other clinical questions for the purposes of this test. Moreover, 2 general practitioners trialed all questions for suitability.

**Table 1 table1:** Data capture on the presearch and postsearch answer screens.

No	Data: purpose	Measurement	Presearch	Postsearch
1	Answer: Decision quality	Select (Yes/no/conflicting evidence/do not know) or type answer depending on the question	Yes	Yes
2	Confidence in answer: impact of the system on answer confidence	How confident are you in your answer? (1=no confidence, 2=a little confident, 3=moderately confident, 4=very confident, and 5=certain)	Yes	Yes
3	Perceived difficulty: relationship with time constraints and answer quality	How would you rate the difficulty of this clinical question? (presearch) and How would you rate the difficulty of the search for evidence for this task? (postsearch). (1=very easy, 2=easy, 3=neither easy nor difficult, 4=difficult, and 5=very difficult)	Yes	Yes
4	Perceived impact of time constraint on decision: relationship with decision quality and confidence	How would you rate the time you had available to make your decision? (1=not nearly enough time, 2=nearly enough time, 3=just enough time, 4=more than enough time, and 5=much more than enough time)	N/A	Yes

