To assess the impact of time constraints on clinical decision quality (RQ-2), the analyses above will be repeated with a breakdown by time constraint category, that is, 3, 6 and 9 min. In addition, an analysis of time-outs by constraint category will be conducted to assess the impact of time constraints on task completion. Time-outs are defined as samples where at the postsearch answer stage (1) the task timer reaches the constraint duration and (2) the participant provides no evidence to support their answer. It is assumed that in a time-out scenario, the participant was unable to complete the task. Significant differences by time-constraint category will be analyzed using the chi-square analysis. An analysis of variance (ANOVA) will be performed across confidence, difficulty, participant-perceived time impact assessments (impact of time on answer, evidence capture, and stress), and search behaviors, such as SERP dwell time, number of queries issued, number of documents opened, and the quantity of evidence items selected. To gain an understanding of the impact of providing a time constraint on the decision-making process, both the average time to search and the average proportion of available search time used will be evaluated and compared for the different task-timing samples. Tombros et al [67] used this proportional figure as a further gauge of participant stress and it can be compared with the reported stress by the participants.

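### Pre-to-post confidence is a paired 5-point ordinal rating, but the planned chi-square, as worded, ignores pairing, category order and the 16 answers per participant

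*Protocol article*

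**What the plan says.** Under Procedures (In Stage 2) the design is paired by construction: "The participant must complete the same 16 tasks in the same order as stage 1". Table 1, row 2, collects confidence on both the presearch and postsearch screens with one ordered item: "How confident are you in your answer? (1=no confidence, 2=a little confident, 3=moderately confident, 4=very confident, and 5=certain".

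For RQ-1, the Statistical Analyses section assesses pre-to-post change in confidence thus: "confidence in their answers will be assessed presearch and postsearch to identify any significant changes relating to search intervention, also using chi-square analysis". The word *also* points to the sentence just before it, which concerns independent groups: "To assess any differences between the participant groups (nurses, doctors, and students), a Chi-square analysis will be performed". Earlier in the same paragraph a paired test is chosen for correctness, with the pairing given as part of the reason: "the McNemar test will be employed because it is a nonparametric test suited to a binary result, with samples taken at 2 points in time".

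The section then repeats the RQ-1 analyses by time limit (RQ-2) and runs a similar set by search system (RQ-3). The sample size rests on correct answer rates only; no power or target shift is stated for confidence.

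**The concern.** The paragraph recognises that correctness is measured twice on the same unit and picks a test to suit. Confidence is measured twice on the same unit as well, but receives the test just used for nurses, doctors and students. A Pearson chi-square of stage by confidence level has three mismatches with these data:

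- It assumes that presearch and postsearch ratings are independent samples.
- It asks whether the two distributions differ in any way. A wider spread with no average gain can be significant, and the statistic carries no direction.
- It counts up to 1536 independent ratings per stage, although 96 people supply them.

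What is at stake is the statement that search changed clinicians' confidence, overall and by time limit and system. Its p-value may be too small or too large, and a modest real gain may be missed in the smaller breakdowns.

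**Working it through.** **The plan's own figure.** The sample size uses "a 2-sample, 2-sided equality", "setting statistical power to 90%, error rate to 5%, and equal sample sizes per cohort". For 40% against 50%:

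n = (1.960 + 1.282)² × (0.40×0.60 + 0.50×0.50) / 0.10² = 10.51 × 0.49 / 0.01 ≈ 514.9.

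The stated 514 is reproduced (519 with a pooled variance). It concerns correct answers and says nothing about confidence.

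**Pairs available for confidence.** 96 × 16 = 1536 before discards; 1536 / 3 = 512 per time limit, about 512 / 96 = 5.3 per participant.

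**Assumptions (none is in the article).** Latent normal scores cut into five categories (equal shares unless stated); pre/post correlation 0.5 (range 0.3 to 0.7); shift in latent SD units; between-participant SD of change either 0 or 0.3. A shift of 0.10 SD is about 0.11 points on the 5-point scale when category shares are unequal (cumulative 15, 40, 70 and 90%).

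**Why the error rate can move either way.** On the latent scale at correlation 0.5, a pre-to-post difference has variance 2(1 − 0.5) = 1 within a participant. The ordinary chi-square acts as if it were the sum of the two marginal variances. The ratio of actual to assumed variance of the mean change is:

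- Independent pairs: 1 / 2 = 0.50, so too few rejections.
- SD of change 0.3, all tasks: (1 + 16×0.09) / (1 + 1.09) = 2.44 / 2.09 = 1.17, so too many.
- SD of change 0.3, one time limit: (1 + 5.3×0.09) / 2.09 = 1.48 / 2.09 = 0.71, again on the conservative side.

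**Simulated rejection with no average shift, 1536 pairs, nominal 5%.**

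- Chi-square, independent pairs: about 3% (correlation 0.3), 2-3% (0.5), 2% (0.7).
- Chi-square, SD of change 0.3: about 11-18% across runs. Part of this excess arises because between-participant variation widens the postsearch distribution, which a chi-square also detects.
- Signed-rank on all pairs, ignoring participant, SD of change 0.3: 14-21%.
- Participant-level test, SD of change 0.3: 4-6%.

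**Simulated power, correlation 0.5.**

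| Setting | Shift | Chi-square | Signed-rank on participant means |
|---|---|---|---|
| 1536 pairs, independent | 0.10 SD | 52% | 92% |
| 1536 pairs, independent | 0.15 SD | 95% | 100% |
| 1536 pairs, SD of change 0.3 | 0.10 SD | 59% | 65% |
| 1536 pairs, SD of change 0.3 | 0.15 SD | 90% | 94% |
| One time limit (512), both assumptions | 0.15 SD | 33-36% | 68-83% |

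The chi-square powers in the third and fourth rows are not adjusted for its inflated error rate. In the last row, runs with unequal category shares put the chi-square at up to 39%.

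**Sensitivity to correlation (independent pairs).** At 1536 pairs and 0.10 SD, chi-square against signed-rank on pairs: 55% vs 88% (0.3), 52% vs 94% (0.5), 50% vs 100% (0.7). At 512 pairs and 0.15 SD, against the participant-level test: about 40% vs 76% (0.3) and 31% vs 97% (0.7).

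**The case against.** **The variant is not named.** The text says only chi-square analysis, and paired chi-square tests (Stuart-Maxwell, Bowker) exist. That is fair: an unpaired 2×5 table is the natural reading, given the preceding sentence and the naming of McNemar elsewhere, but it is not stated. A paired chi-square would restore the pairing and still ignore category order and the 16 answers per person. In the same simulations Stuart-Maxwell reached about 69% at 512 independent pairs and 0.15 SD, against about 85% for the participant-level test. With SD of change 0.3 and all tasks, it rejected more than 20% of the time without an average shift. The wording needs repair on either reading.

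**A reader might infer that the test forfeits most of its power.** The figures do not support that in general. At full sample and 0.10 SD about half or more is kept, and from about 0.15 SD little is lost. With between-participant variation the full-sample gap at 0.10 SD is only 59% against 65%. A loss of about half or more belongs to small shifts within one time limit, or to very small shifts overall.

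**A reader might also infer that the RQ-2 analysis is a one-way ANOVA without a participant factor.** The text, "An analysis of variance (ANOVA) will be performed across confidence, difficulty, participant-perceived time impact assessments", names no form. The task-order section describes a within-subject design for system and time, and the closing paragraph of the analyses names a repeated-measures ANOVA for confounders. That charge has no basis in the article.

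**Importance.** Confidence is in none of the three research questions, is not the decision-quality measure and does not drive the sample size. This stands and limits the weight of the point.

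**Conclusion.** The point holds in a limited form. The article names a test for pre-to-post confidence that, as worded, suits neither the pairing, nor the ordering, nor the repeated answers per participant, and it departs from the paragraph's own reason for using McNemar. The test cannot by itself establish that confidence rose.

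The numerical consequences depend on assumptions the article does not supply. With all tasks, the error rate may lie below nominal (about 2-3%) or above it (about 11-18%), depending on how much participants differ in their change. The power loss is material for small shifts within a time limit and slight at full sample from about 0.15 SD. No main conclusion of the study depends on this analysis, but the remedy is specific and cheap enough to be worth making.

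**What to change.** In the RQ-1 paragraph, replace the chi-square for pre-to-post confidence with one of:

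- a Wilcoxon signed-rank test on the 96 participants' mean post-minus-pre change; or
- a cumulative-logit mixed model with stage as a fixed effect (time limit and system added for the breakdowns) and random effects for participant and question.

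Use the same choice in the time-limit and search-system breakdowns, and report the direction and size of the change with an interval. A signed-rank test on all pairs is not a substitute, because it ignores the participant.

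The cost is a change of analysis wording, with no new data. Each option has a small downside: averaging treats the five levels as equally spaced, and the model assumes proportional odds, which should be checked.
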